### 27.3. Research collaboration with Denmark

The ERIC-PPCI trial will be conducted in collaboration with [name] [name] (Aarhus University, Denmark), who is CI of the Effect of RIC on Clinical Outcomes in STEMI Patients Undergoing pPCI (CONDI-2) trial (NCT01857414).

The CONDI 1 trial (CI [name]) was the first to successfully demonstrate a beneficial effect of RIC in 142 STEMI patients undergoing PPCI in terms of increased myocardial salvage and smaller MI size , effects which were present 6 months later in terms of improved LV systolic function . A €3.0 million research grant has been awarded by the Danish Research Council to investigate the effect of RIC on 12 month clinical outcomes in STEMI patients undergoing PPCI.

The results of ERIC-PPCI and CONDI 2 will be combined in order to maximise power to assess the impact of RIC on clinical endpoints.

The ERIC-PPCI and CONDI 2 trials will each have a separate DSMC and TSC although there will be an opportunity for the these committees to contact each other if required.

A combined and independent Endpoint Validation Committee will review death, HHF, stroke and MI from both trials.

## 28. Hypothesis

Remote ischaemic conditioning improves long term clinical outcomes (cardiac death and hospitalisation for heart failure) at 12 months in STEMI patients undergoing PPCI.

## 29. Endpoints

### 29.1. Primary endpoint

To investigate whether RIC reduces the combined primary endpoint rate of cardiac death and hospitalisation for heart failure (HHF) at 12 months in STEMI patients undergoing PPCI.

#### 29.1.1. Definition for cardiac death

All deaths where there is no clinical or post mortem evidence of a non-cardiac aetiology.

#### 29.1.2. Definition for hospitalisation for heart failure

This will include both heart failure during the index hospitalisation and re-hospitalisation for heart failure. Hospitalisation will be defined as a treatment occurring in hospital. Heart failure will be judged to be present on symptoms (at least one of the following: new or worsening dyspnea, orthopnea, paroxysmal nocturnal dyspnea or increasing fatigue/worsening exercise tolerance) and signs (one of the following: new pulmonary oedema by chest X-ray in the absence of a non-cardiac cause, crepitations believed to be due to pulmonary oedema, and use of loop diuretics to treat presumed pulmonary congestion).

### 29.2. Secondary endpoints

To investigate whether RIC can affect the following secondary endpoints below:

5. Rates of cardiac death and HHF at 30 days. This data will be collected at the 6-8 weeks post-randomisation follow-up.
6. Rates of all-cause death, repeat coronary revascularisation, reinfarction, stroke at 30 days and 12 months. This data will be collected at the 6-8 weeks and one year post-randomisation).
7. Quality of life at 6-8 weeks and 12 months (EuroQol EQ-5D-5L) (for an example EQ-5D-5L see [Appendix 3](#))

### **Biomarkers substudy (400 patients at selected sites)**

8. MI size on 48 hour area-under-the-curve (AUC) hsTrop T and CK-MB

### **MRI substudy (250 patients at selected sites)**

9. MI size on 6 months cardiac MRI (new late gadolinium enhancement expressed as a percentage of the LV mass).
10. Microvascular obstruction on cardiac MRI (hypodense area on late gadolinium enhancement).
11. Myocardial salvage index (AAR [T2 weighted imaging or angiography jeopardy score] subtract final MI size).
12. LV remodelling on 6 month cardiac MRI scan:
  - index LV end-diastolic and end-systolic volumes
  - LV ejection fraction
  - LV mass and wall thickness

### **Coronary Physiology substudy (180 patients at selected sites)**

13. Index of microcirculatory resistance (IMR) during and on completion of PPCI

### **Thrombosis substudy (all patients recruited at Lister Hospital)**

14. Thrombotic status pre and post-PPCI
15. Change in thrombotic status pre and post intervention
16. Differences in ECG ST-resolution and clinical outcomes

### **Myosin C substudy (24 patients at Barts Heart Centre)**

14. MI size on 48 hour area-under-the-curve (AUC) Myosin C

#### **29.2.1. Definition of stroke**

Stroke is defined as a focal, central neurological deficit of cerebrovascular cause lasting more than 24 hours or is interrupted by death within 24 hours. Definition of reinfarction

Reinfarction is defined as an acute MI that occurs within 28 days of an incident or recurrent MI. The ECG diagnosis of suspected reinfarction following the initial MI may be confounded by the initial evolutionary ECG changes. Reinfarction should be considered when ST elevation  $>0.1$  mV recurs, or new pathognomonic Q waves appear, in at least two contiguous leads, particularly when associated with ischaemic symptoms for 20 min or longer. Re-elevation of the ST-segment can, however, also be seen in threatened myocardial rupture and should lead to additional diagnostic workup. ST depression or LBBB alone are nonspecific findings and should not be used to diagnose reinfarction.

In patients in whom reinfarction is suspected from clinical signs or symptoms following the initial MI, an immediate measurement of cTn is recommended. A second sample should be obtained 3–6 h later. If the cTn concentration is elevated, but stable or decreasing at the time of suspected reinfarction, the diagnosis of reinfarction requires a 20% or greater increase of the cTn value in the second sample. If the initial cTn concentration is normal, the criteria for new acute MI apply.

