**Secondary clinical endpoints:**

- Myocardial infarct size at day 3 (72 hour area under curve serum creatinine kinase)
- Left ventricular function on day three and three-six months post pPCI (Echocardiography)
- Re-infarction or recurrent infarction, stroke and unplanned coronary revascularisation at one year (New admission)
- Quality of life at 6-8 weeks and 12 months (EuroQol EQ-5D-5L)

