- Quality of life at 6-8 weeks and 12 months (EuroQol EQ-5D-5L)

All these outcomes are relevant to STEMI patients and have the potential to change clinical practice.

- **Endpoints**

An independent end-point committee will adjudicate primary and secondary clinical endpoints.

- **Primary clinical endpoint**

- Cardiac mortality and HHF at one year

- **Secondary clinical endpoints**

- Myocardial infarct size at day three (72 hour area under curve serum creatinine kinase). Furthermore, TnT in a subset of patients (Aarhus, Aalborg, Belgrade)
- Left ventricular function on day three and three months post pPCI (Echocardiography)
- Myocardial re-infarction/recurrent, stroke and revascularisation at one year
- Persisting ST-segment elevation on ECG 90 min. after primary PCI

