### **Heart failure**

*Validation categories:* HHF; Non-HHF

- During index admission, New admission or unscheduled outpatient clinic visit \*\*
- Symptoms, signs and results of diagnostic test need to be assessed by a medical doctor.

[figure not shown]

\*According to ESC guidelines for diagnose and treatment of acute and chronic heart failure 2012. European Heart Journal (2012) 33, 1787-1847 and “2014ACC/AHA Key Data Elements and Definitions for Cardiovascular Endpoint Events in Clinical Trial”. Circulation.2015;132:302-361

Please note:

- Patients with cardiogenic shock will fulfil the definition of heart failure.
- That acute heart failure developed prior to randomisation should not be considered an event. Neither chronic heart failure diagnosed prior to randomisation.
- That initiation or increment of these drugs due to hypertension is NOT an event. The independent end-point committee will subsequently confirm the diagnosis.

Encounter type:

**In-hospital:** An event where the patient is admitted to the hospital with a primary diagnosis of HF where the length of stay is at least 24 h (or extends over a calendar date if the hospital admission and discharge times are unavailable), where the patient exhibits new or worsening symptoms of HF on presentation, has objective evidence of new or worsening HF, and receives initiation or intensification of treatment specifically for HF.

**Unscheduled outpatient clinic:** An event where the patient has an urgent, unscheduled office/practice/ED visit for a primary diagnosis of HF but is not admitted to the hospital, where the patient exhibits new or worsening symptoms of HF on presentation, has objective evidence of new or worsening HF, and receives initiation intensification of treatment specifically for HF, with the exception that changes to oral diuretic therapy do not qualify as initiation or intensification of or treatment.

- **Secondary endpoints are defined according to the following standard operating procedures:**

For the secondary endpoint, we are interested in those MIs occurring outside the setting of any future elective PCI procedure.

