**SOP for Diagnostic and clinical indications of MI \*, More than 48 hours after index pPCI**  
**Event report in Condi 2**

*Validation categories:* MI ; No MI

[figure not shown]

\*Modified from: "Third universal classification of myocardial infarction". European Heart Journal (2012) 33, 2251-2567 and "2014 ACC/AHA Key Data Elements and Definitions for Cardiovascular Endpoint Events in Clinical Trial". Circulation.2015;132:302-361

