## ○ Secondary Objectives

To determine the effects of RIC on:

- Rates of the individual components of the primary endpoint at 12 months
- Rates of the combined endpoint as well the individual components of cardiac death and/or HHF at 30 days.
- Rates of the individual endpoints of all-cause death, repeat coronary revascularisation, reinfarction, stroke at 30 days and 12 months.

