and Kaplan-Meier curves will be produced. The time scale used for survival analysis will be time to the primary endpoint since randomisation. Participants will be censored if they die of a non-cardiac cause, are lost to follow-up, withdraw from the study, or at 12 months after randomisation. The assumptions underlying the Cox model will be assessed and if there is clear non-proportionality hazard ratios will be presented separately for the relevant time periods.

In addition risk differences at one year, again stratified by trial, will also be calculated together with 95% confidence intervals.

- **Analysis of Secondary, and Other Efficacy Endpoints**

- Cardiac death and HHF at 30 days**

The RIC and control arms of the trial year will be compared on rate of the first occurrence of cardiac death or HHF up to 30 days following randomisation. Hazard ratios and 95% confidence intervals will be calculated using Cox proportional hazards modelling, stratified by trial, and Kaplan-Meier curves will be produced. The time scale for analysis will be time since randomisation. Participants will be censored if they die, are lost to follow-up, withdraw from the study, or at 30 days after randomisation. The risk difference stratified by trial together with 95% confidence intervals will also be calculated.

- Individual components of cardiac death and HHF at 30 days and 12 months**

Survival analysis will be used to examine the individual components of the composite outcome, using the same methods as outlined above.

- All cause death, repeat coronary revascularisation, reinfarction, stroke at 30 days and 12 months**

Survival analysis will be used to examine each of these clinical outcomes and MACCE (all-cause death, repeat coronary revascularisation, reinfarction, or stroke) using the same methods as outlined above.

- Repeat HHF and cardiac death**

In order to take account of recurrent HHF in patients while also accounting for the competing mortality, a parametric joint frailty model will be used for

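### ERIC-PPCI's 28-day definition of reinfarction conflicts with the 12-month reinfarction and MACCE endpoints that the SAP pools with CONDI-2's one-year MI endpoint

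*Supplement*

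**What the plan says.** **ERIC-PPCI protocol version 5.0.** Section 29.2.1, where the reinfarction text runs on from the stroke definition, says: "Reinfarction is defined as an acute MI that occurs within 28 days of an incident or recurrent MI". Section 29.2 lists as a secondary endpoint: "Rates of all-cause death, repeat coronary revascularisation, reinfarction, stroke at 30 days and 12 months".

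**Combined SAP version 3.** Section 2.2 sets the objective "Rates of the individual endpoints of all-cause death, repeat coronary revascularisation, reinfarction, stroke at 30 days and 12 months". Section 5.4.3 analyses these outcomes by survival methods stratified by trial, and adds "MACCE (all-cause death, repeat coronary revascularisation, reinfarction, or stroke". The SAP gives no definition of reinfarction.

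**CONDI-2 protocol version 10.** The body lists "Myocardial re-infarction/recurrent, stroke and revascularisation at one year", and the synopsis has "Re-infarction or recurrent infarction, stroke and unplanned coronary revascularisation at one year (New admission". The operating procedure for MI is headed "More than 48 hours after index pPCI". The text introducing the secondary endpoint procedures says "we are interested in those MIs occurring outside the setting of any future elective PCI procedure", and a separate procedure labels procedure-related MI as outside the secondary outcomes.

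**Data collection and adjudication.** ERIC-PPCI sections 36.1 and 36.3 record MI in hospital, at 6-8 weeks and at 12 months. Section 29.3 names MI and reinfarction as separate items for validation, and has one blinded committee validate MI from both trials.

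**The concern.** A 28-day window cannot serve a 12-month endpoint. Under section 29.2.1 a patient whose first new MI comes at month 5 has no reinfarction, although a further MI within 28 days of that one would count. CONDI-2 counts both kinds to one year. The SAP combines the two under the narrower of the two terms and does not say which events qualify. Two statisticians following the documents could produce different 12-month reinfarction and MACCE results. If the choice were made after unblinding, it would be a post-hoc endpoint decision.

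**Working it through.** The plan states no MI rate, sample size or power for this endpoint, so it has no figure to reproduce. The check sets the windows side by side and then sizes the possible omission.

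1. **Windows as written, counted from the index event.** ERIC-PPCI: day 0 to day 28, plus 28 days after any later MI. CONDI-2: after 48 hours to one year, going by the heading of its MI procedure.
   - They overlap from day 2 to day 28, which is 26 of the 28 UK days (26/28 = 93%).
   - They differ before 48 hours and after day 28.

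2. **Effect at each analysis time.**
   - At 30 days, the cap removes only days 29 and 30 from the UK data.
   - At 12 months, the UK window covers 28/365 = 7.7% of follow-up after the index MI, apart from the short windows opened by later MIs. The UK 12-month result would then add almost nothing to the 28-day result.

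3. **UK weight in the pooled analysis** (SAP section 2.3): 2,800 of 5,400 patients, 2,800/5,400 = 51.9%.

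4. **Share of pooled 12-month MIs omitted on the literal reading.** Assume equal MI rates in the two trials, and let f be the fraction of 12-month MIs after day 28. The documents do not give f, so a range is shown. Omitted share = 0.519 × f, ignoring the few MIs that would count because they closely follow a late MI.
   - f = 20%: about 10%
   - f = 50%: about 26%
   - f = 80%: about 41%

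5. **Share omitted if the committee-validated MI variable is used to 12 months:** 0%.

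6. **Precision.** With equal arms and few events, the standard error of a log hazard ratio varies roughly as 1/√(events). Dropping 10.4%, 25.9% or 41.5% of events multiplies it by 1/√0.896 = 1.06, 1/√0.741 = 1.16 or 1/√0.585 = 1.31.

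No corresponding figure is given for MACCE. The documents give no component rates, and a patient with an uncounted late MI who also dies, is revascularised or has a stroke would still contribute a MACCE event.

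**The case against.** A reader might infer that UK MIs after day 28 are lost from the pooled analysis. The documents do not show that. MI, not only reinfarction, is collected to 12 months in ERIC-PPCI and validated jointly with CONDI-2, so the common adjudicated item may well be MI. Late events drop out only if the SAP's term is built from the literal text of section 29.2.1. That objection stands, and it makes the omission conditional. It does not remove the conflict. Section 29.3 itself treats MI and reinfarction as different items, the SAP uses the narrower term and sends readers to the trial protocols for detail, and nothing shown says that a late UK MI counts.

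A reader might also infer that the two trials use almost separate time windows. They do not, since nearly all of the UK window lies inside the CONDI-2 window.

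The flowchart for CONDI-2's MI procedure is not shown, so its handling of MIs in the first 48 hours rests on a heading alone. The separate trial SAPs and the data-provision document to which the SAP refers are also not shown and may settle the matter. These points limit certainty about practice, but the SAP that governs the pooled analysis should still carry the definition of its own endpoint.

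Finally, these are secondary endpoints. Each trial applies one definition to both of its arms, the analysis is stratified by trial, and results are also to be reported by trial. That stands too, and it sets the severity.

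**Conclusion.** The contradiction is real and present in the latest versions. A 28-day definition is attached to a 12-month endpoint, and the SAP pools that endpoint with a one-year endpoint under an undefined term. The share of pooled 12-month MIs at risk of omission is 0% if the adjudicated MI variable is used. On the literal reading it is about 10% to 41%, for an assumed 20% to 80% of MIs after day 28 and equal MI rates in the two trials. The 26% at f = 50% is the UK share times one assumed value and should not be read as an estimate.

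The harm is to event counts, precision and the meaning of 12-month reinfarction and MACCE, more than to bias between arms. The 30-day result is little affected by the cap, and the primary endpoint of cardiac death or HHF is not affected. This should be fixed, but it does not threaten the trial's main conclusion.

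**What to change.** Before unblinding:

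- In ERIC-PPCI section 29.2.1, remove the 28-day cap from the 12-month endpoint.
- In the SAP, define one committee-validated recurrent MI endpoint to 12 months for both trials. State its start time and whether procedure-related and elective-PCI MIs count, choosing rules that both trials' existing data support. One workable version is MI more than 48 hours after the index PPCI and outside elective PCI, which matches the CONDI-2 procedures. A start at the index PPCI with no procedural exclusion would conflict with those procedures and might need CONDI-2 events that were not reported.
- Settle at the same time whether CONDI-2's synopsis reference to new admissions restricts the endpoint.
- Use the same definition in MACCE, and report earlier MIs separately where they were collected.

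The cost is protocol and SAP wording. ERIC-PPCI already collects MI to 12 months and the joint committee already validates it, so the late UK events need no new data. The small downside of the 48-hour version is that UK MIs in the first 48 hours leave the pooled endpoint.

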#### **29.2.2. Definition of coronary revascularisation**

Revascularisation is defined as coronary revascularisation by PCI or CABG following index PPCI, excluding staged PPCI.

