### 29.3. Endpoint Validation

The primary combined endpoint, stroke, MI, reinfarction and revascularisation will be validated by an independent combined event validation committee (EVC), which will validate death, HHF, MI and strokes occurring in both ERIC-PPCI and CONDI 2. The EVC will be blinded to the randomised treatment allocation.

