### SOP for clinical indicated coronary REVASCULARISATION (not scheduled at index event) report in Condi 2:

Validation categories: Yes or No

[figure not shown]

\*Modified from: "Third universal classification of myocardial infarction". European Heart Journal (2012) 33, 2251-2567 and "2014ACC/AHA Key Data Elements and Definitions for Cardiovascular Endpoint Events in Clinical Trial". Circulation.2015;132:302-361

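### Repeat revascularisation is pooled, alone and within MACCE, from two trial definitions that differ on planned CABG and are not harmonised

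*Supplement*

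**What the plan says.** **ERIC-PPCI v5, 29.2.2:** "Revascularisation is defined as coronary revascularisation by PCI or CABG following index PPCI, excluding staged PPCI". There is one exclusion, and it concerns PPCI, not CABG. No clinical indication is required.

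**CONDI-2 v10** words the endpoint in three ways:
- Synopsis, secondary endpoints: "Re-infarction or recurrent infarction, stroke and unplanned coronary revascularisation at one year (New admission".
- Endpoint list (6.2), with no qualifier: "Myocardial re-infarction/recurrent, stroke and revascularisation at one year".
- Heading of the operating procedure (6.4): "SOP for clinical indicated coronary REVASCULARISATION (not scheduled at index event) report in Condi 2". The flowchart under it is not shown in the available copy.

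**SAP v3** pools the outcome twice. The secondary objectives (2.2) list "Rates of the individual endpoints of all-cause death, repeat coronary revascularisation, reinfarction, stroke at 30 days and 12 months". Section 5.4.3 adds "MACCE (all-cause death, repeat coronary revascularisation, reinfarction, or stroke) using the same methods as outlined above". Neither place defines the event. The methods carried over are Cox models stratified by trial, plus stratified risk differences.

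**Adjudication.** ERIC-PPCI 29.3 opens by naming revascularisation among the events that the combined committee validates. The same sentence then describes that committee as one "which will validate death, HHF, MI and strokes occurring in both ERIC-PPCI and CONDI 2". Section 27.3 gives the same four events for both trials, and 46.4 speaks only of primary endpoints. CONDI-2 has an independent committee adjudicating its primary and secondary endpoints.

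**The concern.** A procedure already decided at the index event reflects the coronary anatomy found on that day. RIC cannot change that decision. If such procedures count in one trial and not in the other, the pooled hazard ratio for repeat revascularisation has no single clinical meaning, and the relative effect moves towards 1. MACCE takes in the same mixture. A reader comparing the two trials could also take a definitional difference for a real one.

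Stratifying by trial lets the baseline hazards differ but still estimates one common hazard ratio. It does not make the events alike. Reporting by trial leaves the pooled and MACCE estimates as they are.

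**Working it through.** **1. The wordings side by side**

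| Procedure | ERIC-PPCI 29.2.2 | CONDI-2 synopsis | CONDI-2 procedure heading | CONDI-2 6.2 |
|---|---|---|---|---|
| CABG planned at index event | counts | excluded | excluded | not settled |
| PCI staged at index event | excluded | excluded | excluded | not settled |
| Elective procedure arranged later | counts | excluded if unplanned means non-elective | may count if clinically indicated | not settled |
| Unscheduled repeat PCI in the index stay | counts | excluded if the admission bracket is a rule | may count | not settled |

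The first row is the firm difference: both qualified CONDI-2 wordings exclude what ERIC-PPCI includes. The second row is common ground. The last two rows depend on which CONDI-2 wording governs.

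**2. Size**

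The documents state no rate, effect or power for revascularisation or MACCE, so there is no figure to reproduce. What follows is illustration.

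From the documents: planned sizes of 2,800 (ERIC-PPCI) and 2,600 (CONDI-2), so w = 2800/5400 = 0.5185. Each 1% of UK patients with a planned, non-excluded procedure adds 2,800 × 0.01 = 28 events over both arms.

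Assumed, not in the documents: the same control risk p of unplanned procedures in both trials, a true risk ratio of 0.75 on these, no effect on planned ones, and planned procedures forming a share s of ERIC-PPCI control-arm events.

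Planned risk in ERIC-PPCI: q = p·s/(1 − s).

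ERIC-PPCI ratio = (0.75p + q)/(p + q) = 0.75 + 0.25s.

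Pooled ratio = (0.75 + w·s/(1 − s)) / (1 + w·s/(1 − s)); p cancels.

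| s | w·s/(1 − s) | ERIC-PPCI ratio | Pooled ratio |
|---|---|---|---|
| 0 | 0 | 0.750 | 0.750 |
| 10% | 0.058 | 0.775 | 0.808/1.058 = 0.764 |
| 25% | 0.173 | 0.8125 | 0.923/1.173 = 0.787 |
| 50% | 0.519 | 0.875 | 1.269/1.519 = 0.835 |

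**3. Absolute scale**

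The risk difference in ERIC-PPCI is (0.75p + q) − (p + q) = −0.25p, whatever q is. The added events do not dilute it; they only make it noisier. With 2,395 per arm and p assumed at 4%, power for the pooled comparison goes from 0.469 at s = 0 to 0.326 at s = 50%. With p at 8% it goes from 0.774 to 0.595.

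No figure is given for MACCE, because the documents do not state its component mix.

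**The case against.** Several points on the other side stand.

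- **The committee.** A reader of the both-trials lists might infer that the combined committee has no task for revascularisation. The first clause of 29.3 says that it has. What remains is an inconsistent remit, so one rule across both trials is not assured.
- **Incompatible definitions.** A reader might go further and call the definitions incompatible, with CONDI-2 rejecting every elective procedure. That rests on one word in the synopsis. The endpoint list is unqualified, the flowchart is not available, and under the procedure's heading an indicated procedure arranged later could count.
- **The index stay.** That CONDI-2 drops repeat procedures during the index admission rests on one bracket in the synopsis. The same bracket closes a list that includes re-infarction, yet the CONDI-2 procedure for MI starts 48 hours after the index PCI, not at a new admission. The bracket is doubtful as a working rule.
- **Documents not shown.** SAP section 3 leaves details of the combined variables to a parallel document, and the SAP introduction refers to separate SAPs for each trial. A mapping may exist there. The protocols would still differ, and the SAP that governs the pooled analysis states no rule.
- **Size.** Every input except the trial sizes is assumed. ERIC-PPCI 30.1 assumes a 25% reduction only for cardiac death and HHF. If RIC has no effect on revascularisation, there is nothing to dilute.
- **Rank.** These are secondary outcomes, and each trial is randomised.

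It could also be said that staged PPCI was meant loosely, to cover any planned procedure. The sentence names PCI and CABG separately and then excludes only the former, so the text does not support that.

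**Conclusion.** The point holds as a matter of harmonisation. On the latest versions, a CABG planned at the index event is an event in ERIC-PPCI and not under either qualified CONDI-2 wording. SAP v3 pools the two counts, alone and in MACCE, with no common definition, and the committee text does not guarantee that one is applied.

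The consequence is a mixed estimand and some dilution of the relative effect. Randomisation within each trial rules out bias between arms from this source, the absolute risk difference is not diluted, and the primary endpoint is unaffected. The pooled ratios of 0.76 to 0.84 (against 0.75) show direction and rough scale under assumed inputs; they are not an estimate for this trial. This is a worthwhile, inexpensive correction to a secondary outcome.

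**What to change.** 1. In SAP 5.4.3, define repeat revascularisation for both trials, as an outcome and as the MACCE component, as PCI or CABG done on clinical indication and not already scheduled at the index event. State how procedures during the index admission count.
2. Align ERIC-PPCI 29.2.2 with this, so that the exclusion covers any PCI or CABG planned at the index event. Bring the CONDI-2 synopsis, endpoint list and operating procedure to the same wording.
3. Classify ERIC-PPCI procedures as planned or unplanned, blind to arm, under the validation that 29.3 already promises.
4. Reconcile ERIC-PPCI 27.3, 29.3 and 46.4, and name who applies the common rule to CONDI-2 events.
5. As a minor tidy-up, add revascularisation to the post-PPCI event list in ERIC-PPCI 36.3; the schedule in 36.1 already marks it in hospital.

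The cost is wording plus a small blinded reclassification of reported UK procedures. The reported UK revascularisation count will be smaller.
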